### Primary outcome and hypothesis

The main hypothesis is that in adult patients with early-treated PKU, a 4-week period of Phe load does not decrease working memory performance measured at each of the four time points (T1 to T4) using accuracy in the visual n-back task of the TAP [37].

### Secondary outcomes

The study further aims to assess the influence of a 4-week period of Phe load on working memory performance (reaction time, visual n-back task, TAP [37]), inhibition (third condition, Color-Word Interference Test, D-KEFS [39]), cognitive flexibility (fourth condition, Color-Word Interference Test, D-KEFS [39]), intensity of neural activation during the working memory task in the MR scanner (n-back task fMRI), strength of functional connectivity between brain regions related to working memory (resting-state fMRI), and on brain Phe concentrations (MRS). All secondary outcomes will be assessed at all four time points (T1 to T4).

### Other outcomes

The PICO Study will further investigate the influence of a 4-week period of Phe load on cognitive performance, specifically on sustained and divided attention, fine motor control, verbal and design fluency, processing speed, mood (short form of the Profile of Mood States, POMS [41]; Beck’s Depression Inventory, BDI-II [42]) and health-related quality of life (PKU quality of life, PKUQOL [43]). Additionally, the influence of temporarily elevated Phe concentrations on integrity of white matter tracts (DTI) and cerebral blood flow (ASL) will be investigated.

Moreover, the study assesses differences between patients with early-treated PKU and healthy controls in regard to cognitive variables, intensity of neural activation during the working memory task, strength of connectivity between brain regions involved in working memory, and structural brain characteristics.

### Statistical analysis

The calculation of the sample size is based on the primary outcome (accuracy, visual n-back task of the TAP) for the intra-individual comparison within the different groups using a crossover design. The power analysis was done using Stata based on a paired means test. A noninferiority margin of 4% in working memory (n-back task) is regarded as clinically irrelevant. This margin is based on a study with healthy adults presenting a standard deviation of 4% in the accuracy condition of the n-back task [46]. Hence, a performance change in the n-back task of 4% or less would support our noninferiority hypothesis. According to Zimmermann and Fimm (2009), the test-retest reliability of the n-back task is 0.67 [37]. The correlation between two periods will be lower. Therefore, a correlation of 0.5 was assumed for this sample size calculation. Based on reported standard deviations in a n-back task in patients with PKU ranging from 5% to 8% (off-diet: SD = 7.6; on-diet: SD = 5.7 [27]), a standard deviation of 8% is expected (assuming that patients are off-diet during the 4 weeks Phe treatment). Based on these assumptions, the PICO Study will be able to detect noninferiority at a margin of 4%, a power of 80%, and a one-sided alpha level of 0.05, with a sample size of 26 patients. From earlier studies, including patients with PKU in Bern [47], patients with PKU are known to be highly motivated. Still, we might need to compensate for possible dropouts, which are suggested to fall between approximately 18% and 30% in other studies including patients with PKU [24, 28]; therefore, the goal has been set to 30 patients. Additionally, the effect size that would be detectable at different sample sizes and correlations for the comparison of the healthy control group and the experimental group (assuming the same number of controls and patients) was assessed. With a sample size of twice 26 participants and a power of 80%, an effect size of 0.79 could be detected at a two-sided alpha level of 0.05. To match the number of patients, the goal has been set to 30 controls.

Data will be analyzed according to the intention-to-treat (ITT) principle whereby all randomized participants will be analyzed in the randomized group regardless of any protocol violations. Moreover, data will be analyzed in the per-protocol patient set, excluding patients who did not receive the randomized treatment schedule, patients who did not comply with the intervention (i.e., unable to follow all four time points, unable to adhere to the treatment arms), or patients who violated major eligibility criteria (i.e., onset of a pregnancy, onset of a concomitant disease status that could affect primary or secondary outcome).

The primary analysis will be performed in the randomized patient group. As recommended by the CONSORT statement for noninferiority trials [48], the analysis of the primary outcome will be based on the ITT as well as per-protocol patient set. Raw data of the n-back task will be transformed into standardized values using age matched normative data from the test manual. Normality of data will be assessed via graphical representation of data. Linear mixed effects models will be used to calculate the lower one-sided 95% confidence limit of the primary outcome. If the lower limit lies above the noninferiority margin of 4% in both analysis sets, noninferiority will be claimed. The mixed effects model will contain the baseline measurements, the 4 weeks measurements, and an indicator for the treatment and period as fixed effects, and a random effect for participants. All primary and secondary continuous endpoints will be analyzed via this approach. Secondary outcomes will primarily be analyzed in the ITT patient set. Secondary outcomes will additionally be evaluated in the per-protocol patient set. Furthermore, processed neuroimaging data will be compared in a cross-sectional and longitudinal manner. Due to the expected heterogeneity of the patient sample, comparisons will be focused on intra-individual changes of cerebral metabolism and functional integrity (comparison Phe vs placebo). Differences between groups will be investigated by linear mixed models, as described above. For the comparison of baseline values between patients and controls, regular linear regression models adjusted for potential confounders will be used.

One interim analysis is planned for the reassessment of the sample size. Currently no reliable data are available on the correlation between the baseline and 4-weeks measurement and between the two different treatment periods for the n-back test. Therefore, the sample size will be re-assessed after 50% of patients to assure sufficient power. The re-assessment of the sample size will only be based on the observed standard deviations and correlations between baseline and follow-up values and between treatment periods. Observed changes within and between treatment periods will not be displayed, nor will the noninferiority margin be modified. No formal testing will take place; therefore, the alpha-level does not require adjustment.

Simple descriptive statistics will be used for evaluation of questionnaires on adverse events and mood. No formal statistical testing will be performed.

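### The goal of 30 patients absorbs at most 13.3% loss, below the whole 18% to 30% dropout range from which the protocol derives it

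*Protocol article*

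**What the plan says.** All of this stands in the Statistical analysis section of the protocol article.

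- **Method:** "The power analysis was done using Stata based on a paired means test".
- **Margin:** "A noninferiority margin of 4% in working memory (n-back task) is regarded as clinically irrelevant".
- **Correlation:** "Therefore, a correlation of 0.5 was assumed for this sample size calculation".
- **Variability:** "a standard deviation of 8% is expected (assuming that patients are off-diet during the 4 weeks Phe treatment").
- **Result:** the design has "a power of 80%, and a one-sided alpha level of 0.05, with a sample size of 26 patients".
- **Dropout:** after remarking that patients with PKU are highly motivated, the text allows for "possible dropouts, which are suggested to fall between approximately 18% and 30% in other studies including patients with PKU" and concludes: "therefore, the goal has been set to 30 patients".
- **Success rule:** noninferiority is claimed only if the lower confidence limit clears the margin in both the intention-to-treat and the per-protocol set. The per-protocol set leaves out, among others, patients who are "unable to follow all four time points, unable to adhere to the treatment arms".
- **Re-assessment:** the sample size is reviewed after 50% of patients, using only the observed standard deviations and correlations.

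**The concern.** The section prints three numbers (26 needed, 18% to 30% dropout, 30 recruited) and links the last to the other two as a conclusion. They do not fit together. Four spare patients out of 30 is a smaller allowance than even the most favourable dropout rate cited.

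The success rule makes this more than a matter of presentation. A patient who leaves before the fourth visit may still contribute partial data to the intention-to-treat mixed model, but is excluded from the per-protocol set, and that set must also show noninferiority. Exclusions for non-adherence or for eligibility violations come on top of dropout. If losses fall in the cited range, an inconclusive result is more likely than a reader would gather from the 80% and the goal of 30.

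**Working it through.** **Inputs** (Statistical analysis section): SD 8 in each period, correlation 0.5, margin 4, one-sided alpha 0.05, power 80%, 26 patients needed, 30 as the goal, dropout 18% to 30%. A true difference of 0 is assumed here; the article does not state one.

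**1. Reproduce the 26.**

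SD of the paired difference = √(8² + 8² − 2 × 0.5 × 8 × 8) = √64 = 8.

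Normal approximation: n = [(1.645 + 0.842) × 8/4]² = 24.7, so 25.

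Paired t-test: power is the probability that a noncentral t variable with n − 1 degrees of freedom and noncentrality (4/8)√n exceeds the one-sided 5% critical value. At n = 26 this is 79.8%; at n = 27 it is 81.2%. The stated 26 for 80% power reproduces to rounding, so the planning calculation itself is sound.

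**2. What 30 can absorb.**

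Largest tolerable loss = 1 − 26/30 = 4/30 = 13.3%.

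**3. Expected completers at the cited dropout.**

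- At 18%: 30 × 0.82 = 24.6.
- At 30%: 30 × 0.70 = 21.

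**4. Power at those numbers, same inputs.**

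| Completers | Corresponds to | Paired t | Normal approximation |
|---|---|---|---|
| 26 | 13.3% loss | 79.8% | 81.7% |
| 25 | 18%, rounded up | 78.3% | 80.4% |
| 24 | 18%, rounded down | 76.8% | 79.0% |
| 21 | 30% | 71.5% | 74.1% |

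If dropout is treated as binomial and power is averaged over the number remaining, paired-t power is 77.5% at 18% and 71.1% at 30%.

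**5. How likely 26 is.**

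With binomial dropout from 30, the chance of keeping at least 26 is 35% at 18% dropout and 3% at 30%.

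**6. Number needed to expect 26.**

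n/(1 − d): 26/0.82 = 31.7, so 32; 26/0.70 = 37.1, so 38. The common mistaken form n(1 + d) gives 26 × 1.18 = 30.7 (31) and 26 × 1.30 = 33.8 (34). Neither form gives 30 anywhere in the cited range.

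**The case against.** **Local dropout may be lower.** The 18% to 30% comes from other studies, and the protocol first says that patients with PKU, including those seen in Bern, are highly motivated. A loss below 13% may be what the authors had in mind. That is possible, but no lower rate is stated, and the text gives the cited range as its reason for 30.

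**The loss is small at the low end.** This stands. At 18% dropout the fall is about 2 to 3 points, and by the normal approximation power stays at 79–80%. Only towards 30% is it material.

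**The SD is cautious.** With the cited SDs of 7.6 and 5.7 at correlation 0.5, the SD of the difference is √(57.76 + 32.49 − 43.32) = 6.85, and 21 completers would give about 83% power. This limits the practical harm. But the protocol fixed 8% for its calculation, and it says itself that no reliable data on the correlations are available, so the slack cannot be counted on.

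**The re-assessment may raise the number.** It may, but by its stated rule it takes no account of dropout.

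**Stronger readings that the document does not support.** A reader might infer that the stated 80% power is wrong. It is attached to 26 patients and reproduces; the fault is in the step from 26 to 30. A reader might also infer that 30 patients cannot leave 26. The shortfall is one of expectation, since at 18% dropout there is still a 35% chance of keeping 26. Finally, a reader might extend the point to the comparison with healthy controls. That comparison uses baseline values and controls are seen only at T1, so later dropout does not remove its data. With 30 per group the detectable effect is 0.74, better than the 0.79 stated for 26 per group.

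**Conclusion.** The point holds as an error in the dropout allowance. Thirty randomised patients are not expected to retain the required 26 at any rate in the protocol's cited range. Under the plan's own inputs, paired-t power in the per-protocol set is about 77–78% at 18% dropout and about 71% at 30% (normal approximation about 79–80% and 74%), against 79.8% at 26.

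These figures assume a true difference of zero, the planning SD and correlation, and that dropouts are the only patients missing from the per-protocol set. Further per-protocol exclusions would lower power; a smaller SD or a higher correlation would raise it. Neither the motivation remark nor the planned re-assessment, as written, closes the gap.

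**What to change.** In the sample-size paragraph of the Statistical analysis section, do one of the following:

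- state that 30 randomised patients preserve about 80% power only if loss is at most 13%, and give the power at 18% dropout (about 77–78%) and at 30% (about 71%); or
- state an expected loss of 13% or less for this trial and justify it.

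In the paragraph on the interim re-assessment, which now restricts the inputs to standard deviations and correlations, add that the re-assessed number of evaluable patients will be divided by (1 − d), with d the dropout allowance. This needs no treatment comparison, so the existing statement that alpha needs no adjustment is unaffected.

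The cost is one changed sentence in each paragraph and a less favourable power statement. If the sponsor would rather keep 26 evaluable across the cited range, the goal rises to between 32 and 38, that is 2 to 8 more patients.

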## Background

Phenylketonuria (PKU) is a rare autosomal recessive disorder caused by a defective function of the phenylalanine hydroxylase enzyme leading to an impaired conversion of the amino acid phenylalanine (Phe) to tyrosine. Untreated PKU with increased Phe concentrations in the blood and brain during childhood leads to severe irreversible neurological impairment with, e.g., mental retardation, intellectual disability, behavioral problems, or other neurological sequelae such as epilepsy or movement disorders [1]. Newborn screening for PKU was established around 1965, enabling early treatment with a dietary restriction of Phe (low protein diet) and Phe-free protein substitutes (amino acid mixtures) soon after birth. Consequently, the population of adults with phenylketonuria with an absence of neurological disabilities has grown substantially since the early 1980s [1]. Most of these early-treated adult patients live a “normal” life as shown in an earlier study at our center, in which 15% of the adult patients with PKU went to high school or graduated from university [2].

Despite wide agreement on the treatment strategy and target Phe concentrations in childhood and for women during pregnancy, no consensus on safe Phe concentrations in adulthood has been reached so far [3]. Traditionally, the low protein diet had been enforced only during childhood and adolescence, leaving adult patients with PKU “off-diet.” Nonetheless, concerns remain that high phenylalanine levels may still have negative effects in adolescents and adults with PKU [4, 5]. Limited evidence of irreversible neurological damage exists, but over the last decade, observational and cross-sectional studies associated high Phe in early-treated adult patients with cognitive problems [6–8], psychiatric symptoms, and behavioral abnormalities [4–6, 9–13].

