### Participants

Thirty adult patients with early-treated PKU and 30 healthy controls comparable to patients with regard to age, sex, and educational level will be recruited. To achieve comparable groups, patients will be assessed first while consecutively searching for controls that are comparable in their demographics. Patients are eligible for the study if they are 18 years of age or older and have PKU diagnosed after a positive newborn screening and treated with Phe-restricted diet starting within the first 30 days of life.

Patients will be excluded if they did not follow a Phe-restricted diet within 6 months before the study, exhibited Phe concentrations above 1600 μmol/L within 6 months before the study, or have a concomitant disease status that could significantly affect primary or secondary outcomes (e.g., untreated vitamin B12 deficiency).

Female patients of childbearing potential will be excluded if they are not using or not willing to continue using at least one highly efficient method of contraception (Pearl index less than 1) for the entire study duration, are pregnant or intend to become pregnant during the course of the study, or are breast feeding.

Patients and healthy controls will be excluded if they have known or suspected noncompliance; show drug or alcohol abuse; changed medications likely to significantly interfere with cognitive functions; have known or suspected hypersensitivity or allergy to one of the ingredients of the placebo; are unable to follow the procedures of the study, e.g., due to language problems (lack of fluency in German or French); participated in another intervention study within the 30 days preceding and during the present study; or have a condition that interferes with the acquisition of MRI scans.

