During the intervention phase, transient mild cognitive impairments might occur due to an increased Phe load. A similar smaller study with increased Phe load over 4 weeks suggested an impairment in sustained attention as well as lower scores in mood profile but did not report any other mild or serious adverse events [28]. Serious side effects are not to be expected. Neither is hyperphenylalaninemia in adulthood known as a cause of metabolic encephalopathy, nor is there a recognized acute decompensation of PKU [51]. The probability of irreversible adverse events during the progress of the present study is therefore extremely low. Even in adult patients with PKU not following any low protein diet for a long time, only very few cases of serious neurologic events with unlikely causal relationship (some of them probably caused by severe vitamin B12 deficiency) have been described in the literature: 11 cases of spastic paraparesis, three cases of muscle weakness/difficulty walking, and three cases of vision loss [52]. Despite not following any low protein diet for a long time, most adult patients showed improved scores for attention as well as self-reported anxiety and depression after reintroducing a low-protein diet [21, 53].

Neuroimaging has become an indispensable tool to better understand brain regions of susceptibility in metabolic disease and to assess the efficacy of dietary treatment on the brain. Clinicians can benefit from the technologic advancements in neuroimaging, allowing for improved understanding of diseases and ameliorated patient management. Only a limited number of neuroimaging studies have been conducted so far in patients with PKU. This is evident on a cross-sectional level but even more so on a longitudinal level. Hence, conclusive evidence on the influence of Phe on brain structure and function is not available with the current state of knowledge. By combining a broad range of advanced MR-techniques, the PICO Study strives to advance our understanding of the disease PKU and its impact on different properties of the brain. The additional information gained by the neuroimaging results may help to characterize subgroups of patients that benefit or do not benefit from restrictive dietary interventions.

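### The per-protocol set drops patients for disease that begins after randomization, so it can select on an effect of Phe and is a weaker check on noninferiority

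*Protocol article*

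**What the plan says.** Under Participants, the protocol article excludes patients at entry if they "have a concomitant disease status that could significantly affect primary or secondary outcomes (e.g., untreated vitamin B12 deficiency"). This concerns what the patient has when enrolled.

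Under Statistical analysis, the per-protocol set leaves out "patients who violated major eligibility criteria (i.e., onset of a pregnancy, onset of a concomitant disease status that could affect primary or secondary outcome"). The part at issue is "onset of a concomitant disease status that could affect primary or secondary outcome": here the same kind of condition counts when it starts during the trial. The text sets no limit by time of onset, treatment period or cause.

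The same section gives the decision rule: "If the lower limit lies above the noninferiority margin of 4% in both analysis sets, noninferiority will be claimed". It defines ITT so that "all randomized participants will be analyzed in the randomized group regardless of any protocol violations".

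The article also names possible effects of high Phe. The Background cites observational links with "cognitive problems [6–8], psychiatric symptoms, and behavioral abnormalities". The Discussion accepts that "transient mild cognitive impairments might occur due to an increased Phe load", and reports that a similar, smaller Phe-load study "suggested an impairment in sustained attention as well as lower scores in mood profile".

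**The concern.** A patient who was eligible at enrolment and falls ill later has violated no eligibility criterion. The clause turns a baseline condition into a post-randomization event, and the test for exclusion is whether that event could affect the outcomes under study. Because the definition is introduced by i.e., it reads as the rule and not as an example.

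For most illnesses this would be a matter of tidiness. Here the article itself lists cognitive and psychiatric effects among the possible consequences of the intervention. A new disorder caused by the Phe load, if it could affect working memory or a secondary outcome, fits the wording. Excluding that patient removes part of the effect the trial is meant to detect. Blinding does not prevent this: if Phe causes the event, a blinded assessor who applies the rule correctly still removes the Phe-harmed patient.

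At stake is the value of the per-protocol set. It is required alongside ITT as a check on the noninferiority conclusion. A set partly selected on the treatment effect gives less reassurance when it agrees with ITT.

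**Working it through.** **The plan's own figure.** Inputs from Statistical analysis: SD 8%, correlation 0.5, margin 4%, one-sided alpha 0.05, power 80%.

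- SD of the paired difference = √(2 × 8² × (1 − 0.5)) = 8.
- Normal approximation: n = (8 × (1.645 + 0.842) / 4)² = 24.7, rounded up to 25.
- Noncentral t: power is 79.8% at n = 26 and 81.2% at n = 27.

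The stated 26 reproduces closely and is not in dispute. The SD of 8 is carried forward.

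**Shift from dropping affected patients.** Suppose k of n patients lose D points on Phe and the others do not change. The mean loss is k × D / n with everyone kept and 0 once the k patients are dropped. The documents give neither k nor D, so both are assumptions (n = 26).

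| k | D = 8 | D = 15 |
|---|---|---|
| 1 | 0.31 (8% of margin) | 0.58 (14%) |
| 2 | 0.62 (15%) | 1.15 (29%) |
| 3 | 0.92 (23%) | 1.73 (43%) |

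**Chance of passing.** In a simulation of 40,000 trials per row, a share p of patients has a mean loss D on Phe and the rest have a true difference of 0. Paired differences have SD 8. A set passes if its one-sided 95% lower t limit is above −4. Every affected patient is assumed to meet the exclusion rule, which is the worst case.

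| N | p | D | True mean difference | All patients pass | Per-protocol passes | Both pass |
|---|---|---|---|---|---|---|
| 30 | 5% | 8 | −0.4 | 75.6% | 82.8% | 75.1% |
| 30 | 10% | 8 | −0.8 | 65.6% | 81.4% | 65.0% |
| 30 | 20% | 16 | −3.2 | 12.3% | 76.5% | 12.3% |
| 30 | 25% | 16 | −4.0 | 5.7% | 73.7% | 5.7% |
| 26 | 10% | 8 | −0.8 | 60.5% | 75.5% | 59.7% |
| 26 | 25% | 16 | −4.0 | 5.5% | 67.7% | 5.5% |

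The per-protocol mean returns to about 0 in every row. At a true loss equal to the margin, the per-protocol set alone passes far above the nominal 5%. The joint rule stays at or just below the all-patients rate. It cannot exceed it, because a trial that passes both sets has passed the all-patients set.

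**Direction in other cases.** If an illness lowers a patient's score under placebo, that patient's Phe-minus-placebo difference is too favorable to Phe. Dropping the patient moves the estimate against noninferiority. Unrelated illness can strike in either period, so its removal can move the estimate either way.

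**The case against.** A reader might infer that the clause biases the trial's conclusion, or that it always favors noninferiority. The documents support neither. ITT keeps every randomized patient and must pass too, so the clause alone cannot create a false claim. The exclusion also covers onset under placebo and in washout, so the one-way direction holds only for disorders that Phe triggers.

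The clause can also be read more narrowly. Concomitant may have been meant as unrelated illness; the one example under Participants, vitamin B12 deficiency, is an independent confounder. A lower n-back score on Phe is the outcome itself and triggers no exclusion. Mood scales stand under Other outcomes, so low mood alone does not meet the clause: it would have to amount to a disease that could affect working memory or a secondary outcome. The Discussion expects mild, transient effects and no serious ones. Case-by-case classification is commonly left to the SAP.

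Most of this stands and limits the size of the problem. It does not remove it. The text does not say that concomitant means unrelated, and could affect is a broad test. The rule is stated in the article, so the point is not about a detail left to an unseen document.

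**Conclusion.** The point holds as a defect in the definition of the per-protocol set. Where Phe triggers a qualifying disorder, exclusion depends on a treatment effect and moves the per-protocol estimate toward noninferiority. The consequence is a weaker safeguard and a possibly biased per-protocol estimate, not a false overall claim. The containment by ITT assumes that the affected patients' outcomes are still measured and enter that analysis.

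The size cannot be derived from the documents. Over the assumed range of 1 to 3 affected patients in 26, each losing 8 to 15 points, the shift is 0.31 to 1.73 points on a margin of 4. A loss of 15 points is nearly two of the plan's SDs, so the upper end is an illustration and not a forecast. If no such disorder occurs, this mechanism adds no bias. The change is still worth making, because the rule is explicit and the correction is cheap.

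**What to change.** Reword the per-protocol definition in three steps:

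1. Count as an eligibility violation only a condition present before the first dose of the investigational product, even if it is discovered later.
2. Keep patients whose disease begins after the first dose in the per-protocol set, with their data.
3. Allow an exception only where a blinded review, completed before unblinding, classifies the event as clearly due to an external cause unrelated to the investigational product, for example a head injury.

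The exception should turn on cause and not on the type of condition, so that a neurological event with a plain external cause can be excluded while one that might be due to Phe cannot.

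The cost is a short wording change and a brief blinded review. No extra patients or measurements are needed. The downside is that an occasional patient with an unrelated illness stays in the set and adds slight noise.

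### The 4% noninferiority margin is set in raw n-back accuracy but tested after the data are norm-standardized, with no conversion, no named metric and no signed contrast

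*Protocol article*

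**What the plan says.** The primary outcome is working memory, measured "using accuracy in the visual n-back task of the TAP" (Primary outcome and hypothesis). Higher is better, and the hypothesis is that Phe load does not lower it.

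The sample-size paragraph of Statistical analysis sets the margin: "A noninferiority margin of 4% in working memory (n-back task) is regarded as clinically irrelevant". Its basis is also in percent accuracy: "This margin is based on a study with healthy adults presenting a standard deviation of 4% in the accuracy condition of the n-back task". The paragraph explains the margin with the sentence "Hence, a performance change in the n-back task of 4% or less would support our noninferiority hypothesis". The SD is on the same scale: "a standard deviation of 8% is expected (assuming that patients are off-diet during the 4 weeks Phe treatment". With a between-period correlation of 0.5, one-sided alpha of 0.05 and 80% power, this gives 26 patients, raised to 30 for dropouts.

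The primary-analysis paragraph of the same section then says: "Raw data of the n-back task will be transformed into standardized values using age matched normative data from the test manual". After a sentence on checking normality, it introduces the linear mixed model and its lower one-sided 95% limit, and gives the success rule: "If the lower limit lies above the noninferiority margin of 4% in both analysis sets, noninferiority will be claimed".

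**The concern.** The margin, its justification, the SD and the sample size all share one unit, percentage points of accuracy. The transformation sentence puts the data into another unit just before the primary model. The protocol does not say whether the standardized values are z-scores, T-scores or percentiles. It does not convert the 4%, and it does not say that the margin test stays on raw accuracy. An analyst who follows the text in order would fit the model to normed scores and then compare the limit with a number that has no stated meaning on that scale.

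The rule also leaves the contrast undefined and gives the margin no sign. For a higher-is-better outcome and a Phe-minus-placebo difference, the bound should be negative.

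This is the trial's only rule for claiming success. The planned sample-size re-assessment, after half the patients, uses observed SDs and correlations and forbids changing the margin. If those SDs were on a standardized scale while the margin stayed in percent, the recalculated number would mean nothing.

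**Working it through.** **Inputs.** From the sample-size paragraph: margin 4, SD 8, correlation 0.5, one-sided alpha 0.05, power 80%, n = 26, goal 30, paired means test. Assumed here: true difference 0. Also assumed, because the documents do not give it: a linear norm with SD *s* between 4 points (the healthy-adult SD the plan cites) and 8 points (the patient SD the plan expects).

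**1. Reproduce the plan's figure on raw accuracy.**
- SD of the paired difference = √(8² + 8² − 2 × 0.5 × 8 × 8) = √64 = 8.
- Normal approximation: n = ((1.645 + 0.842) × 8 / 4)² ≈ 24.7, so 25.
- Noncentral t: n = 27. Power is 79.8% at 26 and 84.8% at 30.

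The stated 26 lies between the two methods. The sample size is therefore a raw-accuracy calculation and is sound on that scale.

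**2. Convert both margin and data.** On z-scores the margin becomes 4/*s* and the SD of the difference 8/*s*. The ratio is 4/8 = 0.5 whatever *s* is, so power at 26 stays 79.8%. For *s* = 4 the margin is 1 z (10 T) with an SD of the difference of 2 z (20 T). For *s* = 8 it is 0.5 z (5 T) with an SD of 1 z (10 T).

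**3. Standardize the data but leave the number 4 as it is.** One T unit is *s*/10 raw points, so 4 T = 0.4*s*. One z unit is *s* raw points, so 4 z = 4*s*. The SD of the difference stays 8 raw points.

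| Reading of 4 | Norm SD *s* | Raw equivalent | Power at n = 26 | n for 80% power |
|---|---|---|---|---|
| Raw points (as planned) | – | 4.0 | 79.8% | 27 |
| T units | 4 | 1.6 | 26% | 156 |
| T units | 8 | 3.2 | 63% | 41 |
| z units | 4 | 16 | about 100% | – |
| z units | 8 | 32 | about 100% | – |

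On T-scores the number 4 keeps its planned meaning only if *s* = 10, since 0.4 × 10 = 4.

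On z-scores the rule barely discriminates. The standard error at n = 26 is 8/√26 = 1.57. Even at *s* = 4, a true loss of 4 points lies (16 − 4)/1.57 ≈ 7.6 standard errors inside the bound, so it would almost always pass.

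**4. Sign.** Taken literally for Phe minus placebo, a lower limit above +4 with no true difference occurs with probability about 0.002% at n = 26 and 0.001% at n = 30. With −4 the figures are 79.8% and 84.8%. The sample size makes sense only with −4.

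**The case against.** The transformation sentence does not say in so many words that the margin test uses the normed values, and the rule itself is still in percent, which fits a test on accuracy. Normed scores could also serve the comparison of patients with controls. A conversion could sit in an analysis plan that is not shown. All of this is possible. But the sentence stands in the primary-analysis paragraph, directly ahead of the primary model, and no other use for it is given. The protocol's own wording therefore conflicts with its margin, whatever another document may add.

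Some stronger readings are tempting, and the protocol does not support them:

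- **Standardizing by itself invalidates the 80% power.** It does not. Under a linear norm with the margin converted too, step 2 shows power unchanged. The low T-score figures arise only from an unconverted 4, and 26% with 156 patients is one end of an assumed range.
- **The plan really demands a 4-point improvement.** Margins are often written as magnitudes. The hypothesis of no decrease, the sentence explaining the margin and the sample size all point to a tolerated loss of 4 points. The missing minus sign is a wording error and the lesser part of this point.
- **The sentence on a change of 4% or less is a second success rule, applied to the observed change.** It does not say observed. It explains the margin, and the only operative rule is the confidence-limit one.
- **Norming creates false changes when a patient moves into another age band.** That depends on norm tables the documents do not contain.

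**Conclusion.** The point holds. The trial's single decision rule cannot be applied without a choice that the protocol does not make: which scale the 4 belongs to, and for which signed contrast. The consequence ranges from none (raw accuracy, or a linear conversion of the margin) to power of 26% to 63% at n = 26 (4 carried unconverted to T-scores) to a nearly automatic claim (4 carried unconverted to z-scores).

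The standardized-scale figures rest on a linear norm with SD of 4 to 8 points, which is an assumption, and on the plan's paired-means calculation rather than the mixed model. A non-linear norm, or one whose SD differs by age, would leave no single conversion factor. The sample size of 26, raised to 30, is not itself in error.

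**What to change.** Preferred: define the primary contrast as the week-4 Phe-minus-placebo difference in raw n-back accuracy, in percentage points. Claim noninferiority only if its lower one-sided 95% limit is above −4 percentage points in both the intention-to-treat and per-protocol sets. Keep norm-standardized scores as supportive or descriptive. This preserves the margin's justification and the sample size, and costs only wording.

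Alternative: keep the standardized analysis, name the metric, and restate and justify the margin, SD, correlation and sample size on it. This needs the normative SD from the test manual and a new calculation, but no new data.

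In either case, reword the explanatory sentence in the sample-size paragraph so that a true loss of up to 4 percentage points (or its restated equivalent) is what is regarded as clinically irrelevant. Settle the scale before the sample-size re-assessment, so that the SDs and correlations taken from the data are in the same unit as the margin, which may not be modified at that step.
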